### Data Collection

Four types of data are consistently monitored:

*1. Clinic data to ensure matching of intervention and standard care clinics. Masihambisane *staff collect aggregated clinic level data for all study clinics: total patients, women attending antenatal care, HIV tests, results received, and participants enrolled in the study. This allows monitoring of enrollment, attrition, and those receiving PMTCT. Figure 2 shows the flow of participants through the data collection process from entry at the clinic, through the consent process, session attendance and post birth assessment.

**Figure 2 F2:**
[figure not shown]
**Participant flow through RCT**.

*2. Medical record reviews. Masihambisane *staff collect and review the medical records of each participant and extract routine health data including: antenatal weight and height, blood pressure, HIV test results, CD4 count, rhesus factor, syphilis and other sexually transmitted infection test results, haemoglobin/anaemia, tuberculosis, preventative medications used such as AZT and NVP, date of delivery, baby weight and length, birth complications, vitamins dispensed, mother's TB and HIV test results, PCR test results, and immunizations.

*3. In-person interview assessments*. A team of two interviewers is placed at each clinic on a full-time basis to interview WLH after their first antenatal visit and six weeks, six months, and twelve months post-birth. All assessments are confidential, and are administered by a trained research assistant, supported by a computerized mobile phone interview protocol. Mobile phones are less expensive than laptops or PDAs, less likely to be stolen, more user-friendly for research assistants and Peer Mentors, and easily provide management information on the duration and location of assessments, enabling data collection with integrity. The program improves data quality by performing simple logic and range validation as data is entered. Skip patterns are also automated, and sections of the survey can be automatically repeated; for example, to cover the same questions about multiple children or partners. Most important, the phones retain all data when no signal is available and automatically upload data when in range of a signal. Uploads occur approximately every 60 seconds, when network coverage permits. The application is pre-configured with identification information, preventing data submission by unauthorised users. In addition, a compromised handset can be blocked at any time to prevent both data uploads and downloads. Secure Sockets Layering (SSL) is used to ensure that all data transferred between the device and the server is encrypted. Uploaded data is available for review, management and export via the web-based *Masihambisane *data platform. Only senior investigators are able to access the data platform. The servers hosting the data are located in Johannesburg, South Africa, and offer full and redundant data protection and security.

Each of the assessments take between 60 and 90 minutes to complete, and cover family background, health, sexual partnerships and behaviours, disclosure, knowledge about HIV issues, daily routines, alcohol and drug use, general knowledge about child care and infant feeding plans, as well as all process and outcome data.

*4. Quality of the intervention delivery*. All intervention facilitators are trained for two months prior to beginning the project. The training includes review of the intervention manual, provision of prompts and materials to support all session materials, and practice role plays with WLH. Supervision is conducted by supervisors who rotate to each site every two weeks to observe and provide feedback, and supervise weekly group sessions. Senior collaborators provide training on a quarterly basis and supervisors give support to Peer Mentors to help them cope with their own feelings about the difficult situations in women's lives. All sessions are conducted by co-leaders to ensure that all procedures are followed as outlined in the manual.

### Data Analysis

WLH are assessed at six days, six months, and twelve months post-birth. Outcomes are compared to health care data routinely collected for mother and child.

The primary outcome is a composite score calculated as the sum of indices for the presence (1) or absence (0) of maternal and child health and well-being. Indices encompass five domains. 1) **
*Child health status *
**includes birth weight and length being within one standard deviation of World Health Organization (WHO) standards, normal development according to WHO norms for motor milestones, absence of FAS symptoms, and positive parenting as assessed by the Parenting Stress Index short form [39] and a bonding questionnaire [40]. 2) **
*Healthcare and health monitoring *
**include the number of antenatal, postnatal, and HIV-related clinic visits. Monitoring includes understanding CD4 count and adherence to all prescribed anti-retrovirals. 3) **
*HIV transmission-related behaviors *
**include disclosure of HIV test results to partners, requesting partners to test, consistent use of condoms, use of single feeding method until six months, baby testing at six weeks, baby prescribed and administered antibiotics at six weeks, maternal AZT during pregnancy, infant NVP at birth and AZT after birth, and disclosure of baby's status to partner or family. 4) **
*Mental health *

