PMTCT programs typically focus on three biomedical interventions: maternal HIV testing; ARV provision in preparation for and during childbirth; and infant ARV medication adherence for six weeks until infant serostatus is established by PCR testing [5]. While ARV treatment is highly effective, only 21% of pregnant women in LMIC were tested for HIV in 2008, and fewer than half of those testing seropositive received ARV medication [1]. Beginning in 2001 [13], routine PMTCT has been available in South Africa. By 2007/08, 81% of pregnant women attending public antenatal clinics in South Africa had been tested. However, Kwa-Zulu-Natal has the lowest levels of testing at 71% [14]. Of the women tested for HIV, about a third do not receive their test results [3,15]. In 2007, 76*% *of pregnant WLH who did receive their test results received Nevirapine (NVP) during labour, while 57% of infants received NVP at birth [13,16].

Health service coverage for women and children in South Africa is good, as 92% of pregnant women have access to antenatal care [15]. Women generally begin antenatal care prior to the third trimester (54%), and 89% of babies are born in a health facility [15]. While full implementation of all public health innovations takes time [17], South Africa has many components in place to eliminate the vertical transmission of HIV.

However, prevention of HIV transmission and the continued well-being of the mother, child and family involve much more than HIV testing and ARV regimes. Receiving an HIV diagnosis during pregnancy often elicits feelings of anxiety, depression and social isolation [18-20]. Poor mental health and a lack of social support are, in turn, associated with decreased uptake of ARV, decreased adherence to ARV medication, and faster disease progression [21,22]. In addition to decreased social support and mental health, WLH face numerous challenges throughout the perinatal period. Women's antenatal clinic records do not follow them to the delivery centre, requiring the disclosure of HIV status to nurses in order to receive ARV medication.

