## Methods/Design

### Objectives

*Masihambisane *is a cluster RCT to test the effectiveness of Peer Mentor support in addressing health, mental health, and stigma challenges faced by WLH. The challenges of chronic illnesses, mental health symptoms, infant feeding and treatment are confronted by WLH on a consistent, daily basis, therefore no single outcome can definitively validate the effectiveness of this Peer Mentor program. We focus on cumulative change across 15 indicators of maternal and infant health. The health-protective behaviors of WLH are documented over time and compared to the baseline rates. These indicators range in their uptake, for example, 92% of babies receive their vaccinations on time, however, infant HIV testing and receipt of results occurs less frequently.

We hypothesize that WLH and their infants in the intervention clinics, compared to WLH who receive standard PMTCT care, will have:

- higher maternal knowledge about HIV self-management;

- better maternal ARV adherence antenatally and at the time of birth;

- increased HIV testing of their baby at six weeks and receipt of test results;

- adherence to regular health visits and TB testing;

- infant weight of more than 2500 grams at birth with normal growth and development for 12 months;

- greater mental health, social support, and ability to cope with HIV stigma;

- higher rates of HIV testing among sexual partners; and

- higher rates of condom use with partners of serodiscordant HIV status.

In order to achieve statistical significance in the analyses, we need to recruit 1200 pregnant WLH (150 per clinic at 8 clinics) with 600 in the intervention and 600 in the standard-of-care control clinics. Enrollment criteria are: 18 years or older at the time of first assessment, less than 34 weeks pregnant at intake, HIV seropositive, and enrolled in the PMTCT programme at one of the eight study clinics. In addition, prospective participants are asked to indicate their intention to reside in the area for the duration of the study, and they must be able to give informed consent, as judged by the interviewer.

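### The primary composite scores a number of clinic visits, which depends partly on gestation at booking and on illness, while the hypothesis is adherence to regular visits

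*Protocol article*

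**What the plan says.** All references are to the protocol article.

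- **Outcome form (Data Analysis).** The primary composite is the "sum of indices for the presence (1) or absence (0) of maternal and child health and well-being". The Objectives put the number of indicators at 15: "We focus on cumulative change across 15 indicators of maternal and infant health".
- **Visit item (Data Analysis, domain 2).** Healthcare and health monitoring "include the number of antenatal, postnatal, and HIV-related clinic visits".
- **Hypothesis (Objectives).** The intervention arm is expected to show "adherence to regular health visits and TB testing".
- **Entry (Objectives).** A woman must be "less than 34 weeks pregnant at intake". No lower limit is given.
- **Order of events (Recruitment; Data Collection).** HIV testing takes place at the first antenatal visit. Consent and the baseline interview follow at a second meeting. In intervention clinics a Peer Mentor meets the woman and offers enrolment before that meeting; control clinics have no such contact.
- **Illness and HIV care (Design).** Standard care refers women with a CD4 count below 200 or WHO Stage 4 illness for HAART.
- **Model (Data Analysis).** The composite is compared by multilevel models that allow for clustering within woman and clinic. No covariate is named for this comparison. Time of recruitment appears only in the dose-response analysis, without saying whether calendar or gestational time is meant.

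**The concern.** Adherence is visits kept divided by visits due. A count has only the numerator. For antenatal care the missing denominator varies widely between women, because it depends on how early each one books, and booking precedes both consent and the programme. Turning the count into 0/1 with a fixed cut-off does not remove this: the same cut-off is easy for an early booker and hard or impossible for a late one.

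The HIV-related part has a different problem, which is direction. A woman referred for HAART because she is ill can collect more HIV-related visits than a well woman who keeps every appointment, yet the score is meant to express health and well-being.

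Two things are at stake. Part of the primary score varies for reasons the programme cannot influence, which weakens the comparison. And if the arms differ in gestation or disease stage at entry, the score can differ between them without any programme effect.

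**Working it through.** The article gives no visit schedule, no distribution of gestation at entry and no power inputs. There is therefore no stated figure to reproduce, and the numbers below are illustrations on stated assumptions.

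**1. Antenatal count against booking date.** Assumed schedule: every four weeks to week 36, then every two weeks to week 40.

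- Booking at 16 weeks: visits at 16, 20, 24, 28, 32, 36, 38, 40, so 8 are possible.
- Booking at 32 weeks: visits at 32, 36, 38, 40, so 4 are possible.
- With a cut-off of 4 visits, the early booker needs 4/8 = 50% attendance and the late booker 4/4 = 100%. With any higher cut-off the late booker cannot score.
- After entry at 33 weeks, 3 routine visits remain (36, 38, 40), or 5 if visits are weekly from week 36. Late entrants still have visits to keep, but few of them.

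Any cut-off on the raw count has this property. Leaving its value to a fuller document does not resolve the point.

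**2. Dilution, worst case.** Assume 15 equal, independent items with equal effects, of which *k* cannot respond.

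- Difference retained = (15 − k)/15.
- Power = Φ[(1.96 + 0.84)(15 − k)/15 − 1.96], starting from an assumed 80%.
- Sample-size inflation against all items responding = (15/(15 − k))².

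| k | Difference retained | Power | Inflation |
|---|---|---|---|
| 1 | 14/15 = 93% | 74% | 1.15 |
| 2 | 13/15 = 87% | 68% | 1.33 |

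k = 1 corresponds to a single visit index, and k = 2 to separate antenatal and HIV-related indices. Both rows overstate the loss, because the programme promotes attendance and these items can respond in part.

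**3. Bias.** Suppose the share of late bookers differs between arms by Δp, and early and late bookers differ by Δs in their chance of scoring the index. The arm means of the composite then differ by Δp × Δs with no programme effect. Since Δs is at most 1, the shift is at most Δp of a point per index. The article gives neither quantity.

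Whether Δp can differ from zero is a design question. There are four clinics per arm. The matching factors in Design and in Pilot activities do not name gestation at booking or disease stage. Women are recruited after their clinic has been allocated, with Peer Mentor contact before consent in one arm only.

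**The case against.** The strongest reply has four parts.

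*The programme acts on attendance.* Women are encouraged to keep all appointments, sessions are held on routine visit days, and attenders receive R30 for transport. Postnatal visits all fall after entry. This stands. A reader might infer that the visit item cannot respond in late entrants, or that it reflects booking more than the programme. The documents support neither: 3 to 5 antenatal visits remain even at 33 weeks, and no figure allows the two influences to be compared. Nor does the article say that visits are counted over the whole pregnancy; it states no window.

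*The index is 0/1.* A reader might infer that a difference between arms in booking age moves the primary score by whole visits. It does not, since each index adds at most one point per woman. The Background's national figure of 54% starting care before the third trimester does not give the share of late bookers here either, because the trial enrols only PMTCT clients below 34 weeks.

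*Randomisation and matching.* Entry criteria are common to both arms, recruitment was standardised, and clinics were matched on patient characteristics among other factors. Pre-entry variation is therefore mainly noise, and the model allows for clustering. This stands as to the main effect. With eight clinics and enrolment contact that differs by arm, it does not exclude imbalance. The separate analysis of each component would help to show an unresponsive item, but would not correct the primary score.

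*Alcohol.* The composite also scores "absence of FAS symptoms". A woman entering at 33 weeks of an assumed 40-week pregnancy has passed 33/40 = 82.5% of it. Because interviews cover "daily routines, alcohol and drug use", a reader might infer that self-reported drinking since entry should replace the FAS index. The documents do not support that. No hypothesis concerns alcohol use, and women taught about alcohol in the sessions may report it differently from controls. The swap could introduce bias where the present item mainly adds noise.

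**Conclusion.** The point holds for the visit index. A number of visits does not measure the hypothesised adherence. Its antenatal part is partly fixed by gestation at booking, before the programme starts, and its HIV-related part can rise with illness.

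The main consequence is dilution, with power of 74% or 68% as worst-case illustrations. These rest on an assumed 80% starting power and on one or two of 15 equal, independent items being wholly unresponsive. Bias is possible but conditional: it needs gestation or disease stage at entry to differ by arm, and its size cannot be computed from the article.

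The documents do not show that the item is dominated by pre-entry factors, and they give no reason to remove the FAS index. This is a worthwhile, inexpensive improvement to the primary outcome. It does not invalidate the comparison.

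**What to change.** 1. Score the visit index as routine antenatal, postnatal and HIV visits kept, out of those falling due for that woman after enrolment, and fix the 0/1 cut-off on that proportion. This removes the dependence on booking date and the credit for illness visits. It also limits credit for extra attendance linked to the sessions. Take the due visits from the standard-care schedule in force at the clinics.
2. Include gestational age at enrolment as a covariate in the primary model and in the models for the antenatal-visit and birth-weight components. It must already be known for each woman in order to apply the 34-week criterion.
3. Keep the FAS index in the composite. At most, report alcohol use since enrolment as an additional component, noting that reporting may differ by arm.

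**Cost.** Due visits must be derived for each woman. The records are already reviewed, but the article's list of extracted items does not name visit dates or the reason for a visit. The list may be incomplete, so some further abstraction may be needed. For late entrants the proportion rests on few antenatal visits and will be coarse.

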**includes the Edinburgh Postnatal Depression Scale [40] and the General Health Questionnaire. 5) **
*Social support *
**includes an adapted scale from Barrera [41] assessing instrumental, emotional, and childrearing support as well as family, neighbour, and community support for healthy acts. The indices are monitored throughout the intervention and at the final assessment.

Intervention effectiveness is assessed by comparing the composite outcome over 12 months between the intervention and standard-of-care control conditions. These composite scores will be compared using multilevel models, i.e., hierarchical models and random effect models, which account for clustering of repeated assessments within individuals and clustering of individuals within clinics [42]. Multilevel models can be applied to normally distributed and non-normally distributed outcomes, we will choose the most appropriate model based on the data. If data transformations sufficiently normalize the composite outcome, e.g., a logarithmic transformation to reduce skewness, we will fit a linear model. If a normal assumption is not appropriate, we will categorize the data and use a longitudinal logistic regression for binary responses [43] and longitudinal ordinal logistic regression to look for shifts in ordinal response levels between the intervention conditions [44]. In all analyses, clustering within clinic will be taken into account, and multiple imputation methods will be used for missing individual outcome scores [45,46].

While the primary outcome composite score will provide a summary of the overall effectiveness of the intervention program, we will also examine each outcome component for a more detailed interpretation. This will be done using longitudinal logistic regression for binary data, to determine whether, and in what direction, the intervention is associated with changes in each component.

Finally, dose-response analysis will be conducted to test for relationships between the number of intervention sessions attended, as well as time of recruitment, and the composite score. The initial patterns of the outcome measures will be examined through descriptive summaries. If necessary, transformations will be conducted to approximate normality, homogeneous variance and linearity in the model.

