**Methods/Design:**

As part of a cluster randomized controlled trial, WLH are invited to attend four antenatal and four postnatal small group sessions led by a peer WLH (a Peer Mentor). The WLH and their babies are assessed during pregnancy and at one week, six months, and twelve months post-birth. Mobile phones are used to collect routine information, complete questionnaires and remain in contact with participants over time. Pregnant WLH (N = 1200) are randomly assigned by clinic (N = 8 clinics) to an intervention program, called *Masihambisane *(n = 4 clinics, n = 600 WLH) or a standard care PMTCT control condition (n = 4 clinics; n = 600 WLH).

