### Design

Eight rural clinics in Kwa-Zulu-Natal were matched on information collected from clinic surveys and observations regarding client load, patient characteristics, range of services offered, and rural-urban setting. The UCLA team, without first-hand experience of the clinics, then randomized clinics to the intervention or the standard care condition.

Standard care includes: dual therapy for PMTCT, referral to Highly Active Anti-Retroviral Therapy (HAART) for women with CD4 counts below 200 or WHO Stage 4 illness, infant PCR test results by six weeks of age, and co-trimoxazole for exposed infants starting at six weeks of age [36]. The intervention clinics will receive the standard care in addition to Peer Mentor support sessions. Peer Mentors were selected from the local communities, based on their HIV seropositive status and role as positive peer deviants. Peer Mentors were trained to deliver four antenatal and four postnatal small group sessions in the clinics to supplement the PMTCT program. An independent assessment team conducted in-person interviews with WLH during pregnancy, and within six weeks, six months and twelve months post-birth, evaluating each WLH and her baby's health and well-being.

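### With only eight randomised clinics, the planned multilevel models need a small-sample arm test; their usual large-sample tests would give about 9–14% error instead of 5% at assumed ICCs of 0.01–0.05

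*Protocol article*

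**What the plan says.** The Abstract (Methods/Design) makes the clinic the unit of allocation: "Pregnant WLH (N = 1200) are randomly assigned by clinic (N = 8 clinics"), with four clinics and 600 women in each arm. The Design section adds that the clinics "were matched on information collected from clinic surveys and observations" before randomisation, without saying whether the matching formed pairs.

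Under Data Analysis, the primary outcome is a composite sum of 0/1 indices, and "These composite scores will be compared using multilevel models, i.e., hierarchical models and random effect models". If the composite cannot be made roughly normal, longitudinal logistic or ordinal logistic regression is the fallback. The section also promises: "In all analyses, clustering within clinic will be taken into account". It names no estimation method (REML or ML), reference distribution, degrees of freedom or small-sample correction.

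On size, the Objectives section says: "In order to achieve statistical significance in the analyses, we need to recruit 1200 pregnant WLH (150 per clinic at 8 clinics"). No effect size, SD, power, significance level or ICC accompanies this.

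**The concern.** Arm varies only between clinics. With four clinics per arm, the information on the between-clinic variance has 8 − 2 = 6 degrees of freedom, or 3 if four matched pairs are analysed as pairs. A random clinic effect puts that variance into the standard error. If the resulting statistic is then referred to a normal distribution, the variance is treated as known, although it has been estimated from very few clinics. ML adds a second problem, because it underestimates that variance.

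The section works through transformations, fallback models and imputation, yet offers nothing for the small number of clusters, the dominant statistical feature of this design. An analyst following the text could report a primary p-value with two to almost three times the stated error and an interval that is too short. The size sentence points the same way: it ties significance to the number of women, when precision depends largely on the number of clinics.

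**Working it through.** **Inputs from the protocol article.** 8 clinics, 4 per arm, 150 women per clinic, 600 per arm.

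**Assumptions.** Two-sided 5% level; 80% power for detectable effects; ICC from 0 to 0.10; a balanced continuous composite in SD units, measured once and unadjusted; no dropout. The article gives none of these.

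**The plan's own figure.** 8 × 150 = 2 × 600 = 1200 checks as arithmetic. Nothing more can be reproduced, because the inputs behind 1200 are not given.

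**Type I error, closed-form limits** (clinic variance dominant):
- REML with a normal reference: P(|t₆| > 1.96) = 9.8%.
- ML with a normal reference: the variance is scaled by 6/8, so the effective cut-off is 1.96 × √(6/8) = 1.697, and P(|t₆| > 1.697) = 14.1%.
- Four pairs analysed as pairs, normal reference: P(|t₃| > 1.96) = 14.5%.

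**Type I error, simulated.** 300,000 null trials per ICC, random-intercept model, clinic variance truncated at zero:

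| ICC | REML, normal | ML, normal | REML, t with 6 df |
|---|---|---|---|
| 0 | 3.8% | 4.5% | 1.0% |
| 0.001 | 4.8% | 5.8% | 1.5% |
| 0.005 | 7.2% | 9.4% | 2.9% |
| 0.01 | 8.6% | 11.8% | 3.9% |
| 0.02 | 9.4% | 13.4% | 4.7% |
| 0.05 | 9.7% | 14.0% | 4.9% |
| 0.10 | 9.9% | 14.1% | 5.1% |

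A t-test on the eight clinic means with 6 df holds 5.0%.

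**Interval width.** The critical value with 6 df is 2.447. A normal-reference REML interval is therefore 1.96/2.447 = 0.80 of the width it should have when the estimated clinic variance is above zero.

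**Binary fallback.** A rough check (600 logistic mixed-model fits per ICC, one time point, likelihood-ratio test) gave about 7.5% at ICC 0.02 and 10.7% at 0.05. The ordinal model was not simulated.

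**Precision.** SE = √[2 × (ICC + (1 − ICC)/150)/4]. Detectable effects come from the non-central t with 6 df. The design effect is 1 + 149 × ICC.

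| ICC | Design effect | Effective number of women | SE (SD units) | Detectable at 80% power |
|---|---|---|---|---|
| 0.01 | 2.49 | 482 | 0.091 | 0.31 SD |
| 0.02 | 3.98 | 302 | 0.115 | 0.39 SD |
| 0.05 | 8.45 | 142 | 0.168 | 0.57 SD |

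With 3 df the detectable effects are 0.39, 0.49 and 0.71 SD.

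**How much the number of women matters.** Going from 75 to 150 women per clinic multiplies the SE by √[(ICC + (1 − ICC)/150)/(ICC + (1 − ICC)/75)]. The reduction is 15%, 10% and 5% at ICC 0.01, 0.02 and 0.05, but 27% at ICC 0.001.

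**The case against.** The strongest reply is that the defect is not in the text. The article names no Wald z test and no ML fit. A REML model with Kenward-Roger degrees of freedom is itself a multilevel model and complies with the Data Analysis section as written. The choice of degrees of freedom is often left to an analysis plan, and this is a condensed article.

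Much of this stands. A reader might infer that the trial will reject a true null 9–14% of the time. The documents do not support that: the figure needs a normal reference that the article never commits to and an ICC that it never gives, and the upper end needs ML as well.

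A reader might also infer that 1200 women is the wrong number. That cannot be shown without an effect, power or ICC. With t on 6 df, the design gives 82% power for 0.40 SD at ICC 0.02 and 78% for 0.30 SD at ICC 0.01. Nor is it shown that the logistic fallback is worse than the linear model; the rough check shows only that it too is inflated.

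The detectable effects also ignore any gain from matching, baseline adjustment or repeated assessments.

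What does not stand is that this is only an unwritten detail. The article presents the models themselves as what accounts for clustering. Fitted with their usual large-sample tests, they give an anti-conservative primary test at plausible ICCs, and a better method is available at almost no cost.

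**Conclusion.** The point holds in conditional form. With eight clinics, the stated models do not by themselves secure a valid arm test. Under large-sample inference, error at a nominal 5% would be about 9–10% (REML) to 12–14% (ML) at assumed ICCs of 0.01–0.05, with little or no inflation at about 0.001 or below. These figures rest on a balanced continuous composite and on ICCs that are assumptions.

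The size sentence is a secondary matter of wording. The number 1200 is neither confirmed nor refuted, but precision is governed largely by the clinic count unless the ICC is very small.

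**What to change.** 1. In Data Analysis, name a small-sample-valid primary test. Either compare covariate-adjusted clinic means, four against four, by t-test on 6 df, or fit a REML linear mixed model with Kenward-Roger degrees of freedom. Report the matching interval.
2. If the binary or ordinal fallback is used, base the arm test on clinic-level summaries with 6 df.
3. State how the clinics were matched and report a matched version as a sensitivity analysis, with 3 df if the matching formed four pairs. An exact paired permutation test cannot serve as the primary test: with four pairs its smallest two-sided p-value is 2/2⁴ = 2/16 = 0.125.
4. In Objectives, replace the appeal to achieving significance with the effect detectable at 80% power with 8 × 150 women over a stated ICC range. On the assumptions above this is about 0.31, 0.39 and 0.57 SD at ICC 0.01, 0.02 and 0.05 (t with 6 df, single unadjusted measurement).

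The cost is analysis wording and one restated sentence, with no added clinics or women. The price is wider intervals and a less favourable stated sensitivity. If the ICC is very small, referring REML to t with 6 df is also conservative (1.5% at ICC 0.001 in the table above).

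### The primary model and its effect measure are left for the outcome data to decide, and non-normality of individual scores is a poor reason to categorise the composite

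*Protocol article*

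**What the plan says.** The Data Analysis section defines the primary outcome as a sum of indices scored 1 or 0 over five domains, compared between arms over 12 months with multilevel models. The Objectives section gives the size of the score: "We focus on cumulative change across 15 indicators of maternal and infant health".

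On the choice of model, the Data Analysis section says "we will choose the most appropriate model based on the data" and then sets out branches:

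- **Linear branch:** "If data transformations sufficiently normalize the composite outcome, e.g., a logarithmic transformation to reduce skewness, we will fit a linear model".
- **Fallback, binary:** "If a normal assumption is not appropriate, we will categorize the data and use a longitudinal logistic regression for binary responses".
- **Fallback, ordinal:** joined to the binary model by the word *and*, "longitudinal ordinal logistic regression to look for shifts in ordinal response levels between the intervention conditions".
- **A further option at the end of the section:** "If necessary, transformations will be conducted to approximate normality, homogeneous variance and linearity in the model".

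The section also commits every analysis to allowing for clustering by clinic. It does not say which fallback model carries the primary conclusion, or that the choice is made without knowledge of arm.

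**The concern.** The four routes estimate different things: a difference in mean number of indicators, an effect on a transformed scale, an odds ratio at a cut-point, and a cumulative odds ratio. Until the outcome data are seen, the reader cannot know which of these the trial's main comparison will report.

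The trigger is the second problem. The route to categorising opens when the score does not look normal, but the quantity of interest is an arm difference in means of a bounded sum, and that does not rest on normal individual scores at this size. Coarsening the score would discard information without solving a real difficulty. A log is also undefined for a score of zero unless an offset is added.

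At stake are a clearly defined treatment effect, some precision if the fallback is used, and the error rate if the choice is made by people who can see results by arm.

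**Working it through.** **Inputs from the protocol article.** 8 clinics, 4 per arm, 150 women each; about 15 binary indicators. The stated total is consistent: 150 × 8 = 1200 = 600 + 600. The article gives no significance level, power, effect, SD or ICC, so 1200 cannot be derived from it.

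**Assumptions made here.** Two-sided 5% level, ICC 0 to 0.05, and a near-normal score as benchmark.

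**1. Is normality of individual scores needed?** The arm comparison rests on clinic means of about 150 women. Averaging divides the skewness of the within-clinic part by √150 = 12.2, so even an individual-level skewness of 1 becomes about 0.08. What remains is the small number of clinics, and categorising women's scores does nothing for that.

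**2. Information kept by a binary split, independent women.** Efficiency relative to comparing means is φ(c)² / [p(1 − p)], with φ the normal density at cut c and p the proportion below it.

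| Split | Efficiency | Loss |
|---|---|---|
| 50/50 | 0.3989² / 0.25 = 0.637 | 36% |
| 30/70 | 0.576 | 42% |
| 20/80 | 0.490 | 51% |

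At the median, 1200 women carry the information of 1200 × 0.637 ≈ 764.

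**3. Ordered groups, independent women.** Information kept is Σ(φᵢ − φᵢ₊₁)² / pᵢ over the groups. Equal groups keep 0.793 (three), 0.861 (four) and 0.897 (five), losses of 21%, 14% and 10%. Very unequal groups do worse: 10/80/10 loses 38% and 80/15/5 loses 48%.

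**4. The median split in the clustered design.** The variance of a clinic mean, in units of total variance, is ICC + (1 − ICC)/150. The split divides only the second term by 0.637.

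| ICC (assumed) | Before | After | Loss |
|---|---|---|---|
| 0 | 0.00667 | 0.01047 | 36% |
| 0.01 | 0.01660 | 0.02036 | 18.5% |
| 0.02 | 0.02653 | 0.03026 | 12% |
| 0.05 | 0.05633 | 0.05994 | 6% |

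In power terms, suppose the linear model had 80% power: 1.96 + 0.84 = 2.80 standard errors. On a normal approximation, multiplying by the square root of the efficiency gives Φ(2.80√0.637 − 1.96) ≈ 61% at ICC 0, about 72% at 0.01 (efficiency 0.815) and about 78% at 0.05 (efficiency 0.940).

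**5. Type I error if the smallest p-value were reported.** Null simulation, 8,000 runs per ICC: 8 clinics × 150, a 0-15 score at one time point, each candidate analysed by a clinic-level t test on 6 df as a stand-in for the multilevel model.

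| Candidates | ICC 0 | ICC 0.01 | ICC 0.05 |
|---|---|---|---|
| Linear only, named in advance | 5.0% | 4.9% | 5.0% |
| Binary or ordinal | 7.8% | 6.9% | 6.3% |
| Linear, binary or ordinal | 9.7% | 8.1% | 7.0% |
| Adding a log model | 11.4% | 9.0% | 7.3% |
| Adding two more cut-points | 16.5% | 13.3% | 9.7% |

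The cut-points were chosen for illustration; the article names none.

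**The case against.** The strongest defence is that the plan has an order: linear if the score can be made near-normal, categorised otherwise. The trigger is the shape of the distribution, not the treatment effect. A decision on pooled, arm-masked data would inflate the error rate little. This stands, and it means that a reader who infers that the plan does not hold 5%, or that it sets out to take the best of several p-values, goes further than the text. The text allows a choice that follows the results; it does not plan one.

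A reader might also infer that a third or more of the information will be lost. The document does not support that as a property of the plan. The figure belongs to a binary split of a normal score in independent women. The fallback also includes an ordinal model, the design is clustered, and few large clinics make the loss from coarsening smaller, not larger. The benchmark is a normal score, whereas the fallback applies when normality fails, so the true loss could differ. A sum of this many items may well look near-normal, in which case the linear branch applies and nothing is lost.

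Finally, cut-points, the number of levels and a normality criterion are details that an article may leave to a full protocol or analysis plan, neither of which is shown. Their absence is not the point. What remains is what the article does state: the data choose the primary model, and a non-normal score is to be categorised and analysed with two models, neither designated primary.

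**Conclusion.** The point holds in a limited form. The stated rule leaves the primary effect measure open until outcome data are seen, and its reason for categorising is not a good one for a bounded sum compared across clinics of about 150 women.

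The size depends on what happens later. The precision loss arises only if the fallback is used, and for a median split the clustered figures (about 18.5% at ICC 0.01, 6% at 0.05) are more relevant to this design than the unclustered 36%. Inflation to roughly 7-10%, or 10-17% with a log model and extra cut-points, requires selection on unblinded results. All of these figures rest on an assumed ICC, significance level and score distribution. The open effect measure depends on none of them.

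**What to change.** Name one primary analysis now: a linear mixed model on the untransformed composite, reporting the arm difference in mean number of indicators present, with clustering by clinic and repeated assessments within women accounted for. Delete the wording that lets the data choose the model, and remove the log and categorising branches as primary routes. Keep an ordinal model as a named sensitivity analysis.

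If a fallback is to be kept, name one model, state its criterion and cut-points, and apply the rule to arm-masked data. Because allocation is by clinic, clinic labels would need masking too.

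The cost is analysis wording only, with no new data or recruitment. The downside is that the team gives up the freedom to switch models after seeing the score.
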